### **14.3.1 Interval data**

Inter-group comparisons will be performed for all interval data at any measurement point by using the analysis of variance (ANOVA) / T-test (if necessary to perform non-parametric tests -> Kruskal-Wallis test / Wilcoxon-Mann-Whitney U-test). In case of significance of the multiple group comparison, single group comparisons will be performed as post-hoc tests according to Fisher (if necessary to perform non-parametric tests -> Wilcoxon-Mann-Whitney-U-test).

For baseline adjustment, comparisons will be calculated not only using the raw data but also data differences (e.g. data at examination day 2 and 3 minus data at examination day 1) to account for individual variances.

Whenever needed, logarithmic transformation of data will be performed for homogenisation of variances prior to statistical analysis.

Within-group comparisons (e.g. examination day 3 versus day 1) will be conducted using the paired T-test (if necessary to perform non-parametric tests -> Wilcoxon-signed rank test).

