## 10.2 Inclusion criteria

- Healthy, term born infants (GA 37-42 weeks)
- with a normal birth weight (girls: 2.7-5.0 kg, boys: 2.9-5.2 kg),
- not older than 8 weeks of age when entering the study,
- not at high risk to develop an atopic disease (at least one parent or sibling with manifest atopic symptoms of hay fever, asthma or atopic dermatitis) which would require the feeding of an HA formula with hydrolysed protein according to current recommendations,
- and with no metabolic disorders requiring a special diet other than standard non-hydrolyzed IF/FOF.

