### **12.2 Study groups**

If an infant has already been fed with at least one bottle of an accepted standard infant formula (cow's milk based formula with non-hydrolysed protein, no probiotics included), this infant will be recruited to the formula groups. Randomization between the two formula groups will take place immediately according to the prepared center-specific randomisation schedule (example see annex). If the infant is on full breastfeeding at study entry, it will be allocated to the non-randomised reference group. The latest possible inclusion day is at 8 weeks of age.

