### **12.3 Per-protocol- and intention-to-treat-analysis**

The protocol foresees for the formula infants that they reach full formula feeding (FF) after 2 months of age at the latest and for the reference infants that they should stay on full breastfeeding (BF) for at least 4 months. Formula infants should cover all formula feedings during the study duration, i.e. till the infant's age of one year, with study IF/FOF. Deviations from this protocol will result in exclusion from the defined formula and breastfed groups with respect to the intended per-protocol-analysis (PP) after the study's end. Formula infants receiving breast milk beyond the age of two months will be evaluated in the per-protocol analysis as members of a mixed-feeding group (duration and estimated amount of breast milk intake will be recorded and statistically checked). For the intention-to-treat analysis (ITT), all infants having been randomised will be evaluated according to the initial group allocation.

[figure not shown]

## 12.4 Examination day 1

The most important examinations will be performed at 5 examination days throughout the study. Day of study entry is defined as *examination day 1*. Questionnaires will be filled in with data on the mother incl. age, demography and socio-economic status, occupation, general health, nutritional status, delivery etc. Data on the feeding pattern will be collected as well (basal questionnaire). The clinical examination of the infant will include anthropometry but to check for pre-existing illnesses which might interfere with the study also the assessment of atopic dermatitis and other skin symptoms (eczema, urticaria, others) as well as the assessment of respiratory (rhinitis, wheezing, etc.), GI tract (vomiting, colics, diarrhoea) and general symptoms (failure to thrive, irritability, food refusal).

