## 12.7 Further examination days

Repetition of the examinations and further sample drawings are planned for the infant's age of about 2 months (*examination day 2*, stools), about 4 months (*examination day 3*, stools), about 6 months (*examination day 4*, stools) and 12 months, i.e. at study end (*examination day 5*, stools and blood).

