## 14. STATISTICAL ANALYSIS

### 14.1 Basic statistical procedure

Given the reasonably large sample size employing parametrical methods assuming a Gaussian distribution will be appropriate allowing for parametrical tests. If necessary, logarithmic transformations of skewed parameters are performed, e.g. for number of illness days.

The first step in the analysis will be a crude comparison between the two formula groups 1 and 2 testing the group effect (different formula) for

- quantitative variables by analysis of (co-)variance (ANOVA/ANCOVA)
- qualitative variables by Fisher exact test / Chi-test
- time-related variables (e.g. "time to infection") by percental frequency curves according to Kaplan-Meier functions / Mantel-Cox log-rank test

One example is an analysis of variance with two groups (T-test) with the number of febrile episodes per child as the dependent variable and type of supplementation as a categorical independent variable. Another example is a Kaplan-Meier curve / Mantel-Cox log-rank test of the percentage of infants without infection throughout the study.

[figure not shown]

The second step is a series of univariate analyses to identify confounders by testing the possible influence of characteristics of the infants on the outcome parameters (to be expressed as odds ratio (OR) and 95% confidence intervals (CI)). Variables considered as potential confounders are, e.g., gender, birth weight, number of siblings, attendance to daycare, smoking in household, duration of breastfeeding, etc.

The third step is a multivariate analysis to identify interaction variables, i.e. confounders which interact with exposure (feeding active formula or placebo).

The final analysis is aiming at simultaneous control of possible confounders and interaction variables by multiple regression analysis with stepwise variable selection to achieve a model that is parsimonious (has only few variables) but maximizes the proportion of the explained variance across study groups. Stepwise procedure:

- baseline model including exposure and core variables,
- stepwise introduction of two-way interaction terms involving exposure (p value to enter 0.05),
- elimination of variables not involved in significant interactions in the multiple regression model (change in exposure odds ratio < 5%).

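### Section 14.3.1 tests interval data both raw and as differences from examination day 1 without naming the deciding result; one ANCOVA on the day-1 value would be more precise than either

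*Protocol*

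**What the plan says.** Section 14.3.1 (Interval data) sets the test: "Inter-group comparisons will be performed for all interval data at any measurement point by using the analysis of variance (ANOVA) / T-test", with rank tests as the fallback. For baseline adjustment it adds that "comparisons will be calculated not only using the raw data but also data differences", and gives as its example "data at examination day 2 and 3 minus data at examination day 1". It ranks neither analysis above the other.

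ANCOVA appears once, in section 14.1, where the first, crude step compares "quantitative variables by analysis of (co-)variance (ANOVA/ANCOVA"). No covariate is named and there is no link to the day-1 value.

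On timing, section 12.4 reads "Day of study entry is defined as" examination day 1. Section 10.2 admits infants "not older than 8 weeks of age when entering the study", and section 12.2 adds "The latest possible inclusion day is at 8 weeks of age". Examination day 2 is "planned for the infant's age of about 2 months" (section 12.7); the schedule in section 12.12 puts it at week 8 with a one-week window.

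On multiplicity, section 14.3 sets alpha at 0.05. For data expected to differ it corrects over groups and time points. For data assumed equivalent (growth, acceptance, tolerance) it makes no correction.

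**The concern.** There are two separate weaknesses.

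First, the plan produces two p-values for each variable and visit that has a day-1 value, with no rule on which one counts. A reader of the results cannot tell in advance which will be treated as the finding. For growth this works in both directions: a second uncorrected test makes a false safety signal more likely, and without a rule the less precise, non-significant result could be the one offered as reassurance.

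Second, neither analysis uses the day-1 value well. The raw comparison ignores it. The difference subtracts all of it, whatever the correlation with the later value. ANCOVA estimates how much to subtract and costs one degree of freedom.

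The difference at day 2 is also awkward to interpret. An infant entering soon after birth contributes about 8 weeks of change; one entering at 8 weeks contributes almost none.

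**Working it through.** **The plan's own power figure.** The only one is for the primary endpoint (section 10.5): 250 per group, difference 1.0, SD 3.5, alpha 0.05. SE = 3.5 × √(2/250) = 0.313, and 1/0.313 = 3.194. One-sided power = Φ(3.194 − 1.645) = 93.9%; two-sided power = Φ(3.194 − 1.960) = 89.2% (noncentral t: 93.9% and 89.0%). The stated 93% and 89% reproduce. The count of febrile episodes has no day-1 value, so nothing below changes these figures.

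**Precision.** Let rho be the correlation between the day-1 and the later value. The protocol does not give it, so a range is shown, assuming equal variances at both visits. Per-infant variance relative to the raw comparison is:

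- raw: 1
- difference: 2(1 − rho)
- ANCOVA: 1 − rho²

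ANCOVA is below raw for any rho other than 0. It is below the difference for any rho under 1, because 2(1 − rho) − (1 − rho²) = (1 − rho)². For scale, the last column gives n per group for 80% power at an illustrative effect of 0.25 SD, two-sided 0.05: n = 2 × (1.960 + 0.842)² × variance / 0.25².

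| rho | Difference | ANCOVA | ANCOVA ÷ difference, (1 + rho)/2 | n: raw / difference / ANCOVA |
|---|---|---|---|---|
| 0.3 | 1.40 | 0.91 | 0.65 | 252 / 352 / 229 |
| 0.5 | 1.00 | 0.75 | 0.75 | 252 / 252 / 189 |
| 0.7 | 0.60 | 0.51 | 0.85 | 252 / 151 / 129 |
| 0.9 | 0.20 | 0.19 | 0.95 | 252 / 51 / 48 |

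Below rho 0.5 the difference is less precise than no adjustment at all.

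**Two tests at 0.05.** Under the null the raw and difference statistics have correlation (1 − rho)/√(2(1 − rho)) = √((1 − rho)/2). The chance that at least one rejects is 1 − P(|Z1| < 1.96 and |Z2| < 1.96):

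| rho | Correlation of the two tests | At least one rejects |
|---|---|---|
| 0 | 0.707 | 8.3% |
| 0.3 | 0.592 | 8.8% |
| 0.5 | 0.500 | 9.1% |
| 0.7 | 0.387 | 9.4% |
| 0.9 | 0.224 | 9.6% |

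A single pre-specified test has 5%.

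**Variable interval.** In a null simulation of the day-2 visit (4,000 replicates, 250 per group), entry age was uniform over 0 to 8 weeks, day 2 was at week 8, and the correlation was assumed to be 0.9 × exp(−gap/8), with the gap in weeks. Standard errors of the group difference were:

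| Assumed age trend in the measure | Raw | Difference | ANCOVA, day-1 value | ANCOVA, day-1 value, entry age and their product |
|---|---|---|---|---|
| None | 0.0885 | 0.0820 | 0.0723 | 0.0703 |
| 0.25 SD per week | 0.0877 | 0.0973 | 0.0769 | 0.0718 |

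With the trend, the difference becomes the least precise of the four. The last model includes a product term. In this set-up entry age as a plain covariate absorbs the linear trend, so it should return about the no-trend ANCOVA value, 0.072, and most of the gain does not need the product. Each single test rejected in 4.1% to 5.5% of null replicates, so none is invalid alone. At least one of raw and difference rejected in 8.2% (no trend) and 9.2% (trend).

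**Which variables have a day-1 value.** Anthropometry does (sections 12.4 and 13.6). Blood does not: it is drawn at 6 and 12 months (sections 12.5 and 13.4). For stools the protocol disagrees with itself. The synopsis outline takes a sample before study feeding starts and section 13.3 speaks of every examination day. Section 12.5, section 12.7 and the schedule in section 12.12 have stools on days 2 to 5 only. On the latter schedule no difference from day 1 can be formed for flora, pH or sIgA.

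**The case against.** Five points can be made for the plan.

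- **ANCOVA is already named, and section 14.1 ends in a multiple regression.** True, so it would be wrong to say that the protocol omits ANCOVA. But it is named without a covariate. The confounders listed in sections 6.4 and 14.1 include birth weight, which is related to later growth, but not the day-1 value. Section 14.3.1, the only text on baseline adjustment, prescribes something else.
- **The deciding model for secondary variables is commonly left to the SAP.** An SAP could indeed say which result counts. The point is about what section 14.3.1 does prescribe: tests on raw values and on differences. An SAP with one ANCOVA would have to depart from it.
- **Growth is age-standardised.** Section 13.6 uses z scores at actual decimal age, adjusted for age and gender. This removes much of the interval problem for growth. It does not settle which test counts, and it does nothing for measures without such a standard.
- **The size rests on an unknown rho and on equal variances.** Correct. Against the raw test the gain at rho 0.3 is only 9%; the 35% reduction at that rho is against the difference alone.
- **Day 3 and later are less affected.** Intervals from day 1 to day 3 are at least about 8 weeks, so the near-zero interval arises only at day 2.

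A reader might also infer that mixing infants with short and long exposure pulls the early difference between formulas toward zero because change scores are used. The documents do not support that. The mixture comes from the visit schedule and affects raw, difference and ANCOVA analyses alike. Randomisation balances entry age between the two formula groups, so all three estimate the same expected difference. Only comparisons with the non-randomised breastfed group lack that protection.

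**Conclusion.** The point holds as a worthwhile improvement to secondary and safety analyses. For variables with a day-1 value, section 14.3.1 sets two competing tests with no deciding one, and both are less precise than ANCOVA. For rho from 0.3 to 0.7 with equal variances (both assumed), ANCOVA variance is 9% to 49% below raw (1 − 0.91 and 1 − 0.51) and 35% to 15% below the difference (1 − 0.65 and 1 − 0.85). Reading both tests at 0.05 gives an error of about 8% to 10% per variable and visit, and section 14.3 does not cover this pair.

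The variable interval costs precision and interpretability at day 2 for measures that are not age-standardised. It is not a source of bias between the formulas. A reader might extend the point to the main result, or to all stool and immune markers. The primary count and the blood markers have no day-1 value, and the stool variables are affected only if the day-1 sample exists.

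**What to change.** Reword section 14.3.1 so that the deciding analysis is one ANCOVA per variable and visit, with the day-1 value (the z score for growth), age at entry and centre as covariates. Keep the raw and change-score comparisons as description, without decisive p-values. The log transformations already foreseen can stay.

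Do not adjust for weeks on study formula or restrict by it. At day 2 it is close to 8 minus age at entry, so it is nearly collinear with that covariate. It also depends partly on what happens after randomisation, and restriction changes the question.

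Reconcile the synopsis outline and section 13.3 with sections 12.5, 12.7 and 12.12 on whether a day-1 stool sample is taken. Without it, no baseline adjustment of stool variables is possible, and the text should say so.

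The cost is wording. Day-1 anthropometry, age at entry and centre are already recorded, and the sample size does not change. Only the stool baseline could need an extra sample, and then only if the sponsor follows the synopsis.

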### **14.3.2 Ordinal data**

Ordinal data such as regurgitation and vomiting will also be analyzed by using the Kruskal-Wallis / Wilcoxon-Mann-Whitney-U-test. For within-group comparison the Wilcoxon-signed rank test will be used.

### **14.3.3 Nominal data**

Qualitative data, e.g. tolerance data such as stool colour, will be analysed by using contingency table analyses of the coded raw data (Chi-test).

## **14.4 Correlations**

Relationships between single interval data will be tested by regression analysis. If reasonable, logarithmic transformations of the data will be performed for linearisation of data relationships.

## 15. DOCUMENTATION

Case report forms (CRFs, see appendix) shall be used for recording all findings relevant for assessment of the selected parameters (parallel documentation of hospital's patient records).

For each form on which information is entered, the patient's initials, study number, date of birth, sex, and supplementation group shall be entered in the appropriate space. The CRFs shall be neatly handwritten, preferably with a black or blue ink ball-point pen.

Errors must be corrected by drawing a single line through the incorrect entry and writing in the new value positioned as close to the original as possible. The correction must then be initialled and dated by the authorised individual making the change. In no case obliterate, write over, or erase the original entry when making a correction.

As soon as possible after the end of each infant's participation in the study, the CRFs shall be completed and signed by the principle investigator. Copies will be handed over to the local study manager for review of completeness. The investigator will maintain adequate records to enable the conduct of the study to be fully documented.

Protocols, subjects' records, originals of test result reports, formula dispensing logs, correspondence, records of informed consent and other documents pertaining to the conduct of the study must be kept on file by the investigator for a period of time specified by local law for the preservation of hospital subject documents. No study document should be destroyed without prior written agreement between NUMICO Research and the investigators. Should the investigators wish to assign the study records to another party, or move them to another location, NUMICO Research must be notified first.

The investigator shall supply NUMICO Research on request with any required background data from the study documentation or clinic records. This is particularly important when subjects' records are illegible or when errors in data transcription are suspected. In case of special problems and / or governmental queries, it is also necessary to have access to the complete study records, provided that subject confidentiality is protected.

Samples and questionnaires will be blinded in order to maintain confidentiality of trial documents and subject records and data will be maintained under secure conditions. For long term storage of any clinical material consent will be obtained. The investigators assure that subject's anonymity will be maintained. On all documents submitted to NUMICO Research, patients will not be identified by their names, but will be pseudonymized by an identification code, e.g. study number and initials. The investigator will keep a subject enrolment log showing codes, names and addresses. Documents not for submission to NUMICO Research, e.g. subject written consent forms, will be maintained by the investigator in strict confidence.

## **16. CLINICAL MONITORING**

The principal investigator is in charge with guaranteeing continuous monitoring by supervising research nurses and physicians he/she has authorised. All findings recorded during clinical monitoring will be retained for at least 1 year and made available upon request of a professional NUMICO Research representative during a monitoring visit to obtain clinical background information for data evaluation.

## **17. CONFIDENCE AND PUBLICATION**

Any information concerning the products and the test results of the study described above is treated as strictly confidential and it is not permitted to transmit or to publish them without written consent of NUMICO Research Germany. However, upon completion of study and integration of all results in the study report, the investigators may publish the results if the data warrant publication and if the number of study infants is sufficient for valid statistical analysis. Any decision in favour or against publication of study results is left entirely to the investigators. Nevertheless, in order to safeguard against disclosure of confidential information or misinterpretation of data, it is requested by NUMICO that any manuscript(s) for publication, texts of talks, abstracts or papers and similar material will be submitted to NUMICO for review, comment and approval prior to publication. In order to ensure that NUMICO will be able to make comments and suggestions where pertinent, material for public dissemination will be submitted to NUMICO for review thirty (30) days prior to submission for publication or review by a Programme Committee. In the unlikely event of any disagreement, e.g. to incorporate such comments and suggestions, the dispute shall be submitted to an independent third party (expert in this research field) mutually chosen by the parties. Such third party shall decide whether NUMICO's comments shall be included or not in the manuscript(s) and its decision shall be final and conclusive between the parties. NUMICO will reimburse any costs related to such third party assistance. The sequence of publications and the coverage of different aspects will be matter of discussion and common decision of the participating clinicians and NUMICO. It is understood, however, that no publications will occur until the publication of the main article for the study. The investigators may prepare the manuscript(s) with the assistance of NUMICO. Such assistance may include journal selection or writing or editing of the manuscript(s).

## **18. WITHDRAWALS AND DROPOUTS**

Parents have the right to withdraw their infants from the study at any time for any reason. The investigator also has the right to withdraw subjects from the study for medical (or other sound) reasons. It is understood by all concerned that an excessive rate of withdrawals can render the study uninterpretable: therefore, unnecessary withdrawal of subjects should be avoided.

Refusal of specific study assessments or complete withdrawal from the study does not preclude a subject from subsequent evaluation. Unless they refuse, all subjects that have been randomised will be followed up.

If any subject fails to complete the study (withdrawal from the study, e.g. in case of revocation of parental consent, or dropout, e.g. in case of illness of study members\*) the reason should be specified in writing by the supervising physician. If parents decide to withdraw their child from the study without giving any reason this should also be stated. If needed for clarification of dropout or withdrawal reasons telephone interviews are to be planned.

For the intention-to-treat analysis, results will be reported for all subjects as randomised. For the per-protocol analysis, however, withdrawals, dropouts, and non-compliers will be excluded. Furthermore, formula fed infants with partial breastfeeding beyond four study weeks will be evaluated as separate groups (mixed feeding).

In case of >30% missing data of an infant the concerned subject will be excluded from the per-protocol evaluation (dropout because of missing data). The same is true if the specific feeding regimen for an individual is discontinued before the study end (dropout because of violation of feeding regimen). For identification of non-completers as possible non-responders, however, the protocols (CRFs) of those cases should also be carefully checked. Incidental feeding of small amounts of food different from the prescribed feeding regimen will not lead to exclusion (incidental intake of infant tea, glucose electrolyte solution for some hours, or else).

---

\* If patients fall ill during the study period, the main investigator will decide whether the disease requires withdrawal of the patient from the study. This will also depend on the type and dose of drug(s) provided for treatment.

